### Study Setting and Recruitment

The study will be conducted at a single site in the United States. Participants will be recruited verbally by participating clinicians and via community advertising.

### Study Tools

#### Overview

Three tools will be used in the study: PEAR-002b, reSET-O, and EmbracePlus. PEAR-002b is a standalone software app that includes a new set of features designed for use with the reSET-O PDT. The mechanism of action for the combined PEAR-002b and reSET-O treatment is a program of medication dosing support during week 1 of the buprenorphine initiation phase, including psychoeducation, CBT, and CM. During the first week of treatment (ie, the buprenorphine initiation phase) participants are guided through the medication initiation process with psychoeducation to support proper medication use and a self-report withdrawal scale to advise the participant on when to take their buprenorphine. During the use of reSET-O, which occurs in weeks 2 to 4, participants are instructed to complete 4 lessons per week. The EmbracePlus device is a medical-grade smartwatch that will be used to collect physiologic data (eg, heart rate and skin conductance) from participants who agree to use the device.

The smartphones loaned to participants in this study include an installed security feature that blocks downloads of other apps, potentially limiting their market value and thus reducing the risk that the phones will not be returned at the conclusion of the study.

#### PEAR-002b Summary Description

PEAR-002b includes an algorithm designed to support buprenorphine dosing and provide associated therapeutic content related to medication and recovery. Medication dosing recommendations are based on provider input (eg, starting dose) and reported recent substance use. A withdrawal symptom scale based on the Subjective Opiate Withdrawal Scale helps participants identify when to take their medication and how to titrate their medication dose to manage withdrawal symptoms. Development of all features and content was informed by feedback generated through participant interviews and prototype testing sessions.

The PEAR-002b content was designed to maximize the efficacy of buprenorphine treatment by educating participants on the importance of proper buprenorphine use and adherence in recovery. Videos and text-based modules address the following topics: preparing for buprenorphine initiation; recognizing, coping with, and managing common opioid withdrawal symptoms prior to buprenorphine initiation; proper initiation of buprenorphine; techniques for sublingual or buccal dosing of buprenorphine to maximize absorption and therapeutic drug levels; how medication adherence supports treatment goals; misconceptions and stigma pertaining to buprenorphine treatment; proper storage and security of buprenorphine to minimize the risk of diversion; and the mechanism of action of buprenorphine treatment.

#### reSET-O Summary Description

PEAR-002b is designed as an optional feature of the reSET-O PDT, which provides an 84-day course of behavioral treatment for OUD as an adjunct to standard buprenorphine MOUD treatment. The reSET-O PDT delivers behavioral therapy modeled on the Community Reinforcement Approach [21], which is a specific form of CBT designed for patients with OUD [22-24]. The PDT provides therapy through a series of 67 interactive lessons delivered via a patient-facing smartphone app. It also has a web-based dashboard for use by clinicians. A typical therapy lesson consists of a CBT component and skill-building exercises. Therapy lesson content is delivered primarily via written text but may also include videos, animations, and graphics. It also has an optional function that patients can use to set medication reminders. The first time a patient opens the app each day, they are asked to report whether they have taken their buprenorphine. Patients who report not taking it are asked to indicate the reasons for nonuse.

Therapy lessons are divided into “core” and “keep learning” lessons. Core lessons cover key CBT concepts, whereas “keep learning” lessons include more in-depth information on key CBT topics covered in the core lessons, as well as additional topics that may be of interest to patients. Once a core lesson is completed, patients can unlock the next lesson. “Keep learning” lessons can be completed in any order and are accessible once the core lessons are completed.

#### EmbracePlus Summary Description

EmbracePlus is a device worn on the wrist that collects, processes, stores, and wirelessly transmits physiologic parameters to a companion app and monitoring platform. The device consists of an electronic display, display case, wristband, and sensors. The device produces 2 types of data: raw data (high-frequency data recorded by EmbracePlus sensors) and digital biomarkers (computed from raw data using algorithms). Biomarkers aggregated by EmbracePlus (1 value per minute) include pulse rate, pulse rate variability, respiratory rate, blood oxygen saturation, sleep periods, movement, skin conductance, temperature, and wearing time. In addition to collecting physiologic data via its sensors, EmbracePlus enables the user to tag specific events by pressing a button on the side of the device. Data collected via EmbracePlus flow through the Empatica Care app (a participant-facing app that notifies the participant if action is required and provides a real-time display of digital biomarkers) to Empatica Cloud (for data storage) and the Empatica Care Portal (a web app to manage study participants and monitor digital biomarkers computed by EmbracePlus).

### Ethical Considerations

#### Conduct of the Study

This study will be conducted in full accordance with all applicable policies and procedures and all applicable US federal and state laws and regulations, including the 45 Code of Federal Regulations 46, and the Health Insurance Portability and Accountability (HIPAA) Privacy Rule. Any episode of noncompliance will be documented. The investigator will perform the study in accordance with this protocol and will report unexpected problems in accordance with institutional review board (Advarra IRB Services; approval number Pro00037072) procedures and all federal requirements. Collection, recording, and reporting of data will be accurate and will ensure the privacy, health, and welfare of research participants during and after the study. All participants will be required to sign an informed consent document at the screening visit, prior to the start of any study-specific procedures. The informed consent document will include an overview of the study, including a clear description of all study procedures, potential risks and benefits of participating in the study, and alternatives to participating in the study. Participants have the right to withdraw from the study at any time and for any reason, and all participants are made aware that withdrawal will not affect their routine care.

#### Confidentiality

The anonymity of participants will be maintained. Participants will be identified by their initials and an assigned study number on electronic case report forms (e-CRFs) and other documents submitted to the study monitor. No protected health information will be stored outside of the study clinic, PEAR-002b system, reSET-O, or the encrypted HIPAA-compliant electronic data capture platform. Data collected by the PEAR-002b system will be securely transferred using industry standard encryption to the PEAR-002b backend services, which use a cloud-based infrastructure that serves and communicates with the patient-facing mobile app.

The backend services contain all data and analytics for reSET-O, PEAR-002b, and its clients (participants and clinicians). All data stored by the study devices are hosted and stored by Amazon Web Services (AWS). AWS follows a variety of internationally recognized security standards, such as the National Institute of Standards and Technology SP800-53 and HIPAA. All participant information is automatically encrypted by AWS when it is entered into the system, allowing for secure data transfer (from participant device to clinician device) and storage.

The EmbracePlus and Care apps are compliant with federal regulations, directives, and international standards for medical devices. Empatica Cloud is the infrastructure where the data recorded from EmbracePlus is collected and made accessible via web interfaces and data repositories. Empatica Cloud is HIPAA compliant. Participant data collected via EmbracePlus is securely stored and encrypted within the AWS cloud service.

Participants will be compensated for attending study visits and completing study assessments as follows (all values in US $): baseline clinic visit, $50; weekly study visit (n=4), $20; urine sample (n=5), $10; qualitative interview (n=2), $50; wearable use, $10 per study visit (n=4). Participants also have the chance to receive monetary rewards in the form of digital gift cards, ranging in value from $5 to $100, earned via the use of the CM functionality of the reSET-O study device.

### Study Procedures and Assessments

Prospective participants referred to the study will be screened for eligibility criteria by a research assistant based on the study inclusion and exclusion criteria and clinical documentation of assessments as needed. Diagnoses of OUD will be made by treating clinicians following standard clinical protocols at the study site, based on *DSM-5* criteria. Recruited participants will be given standard screenings in accordance with the assessment schedule. For the convenience of participants, screening and baseline visits may be combined. All participants will be required to sign an informed consent form at the screening visit, prior to the start of any study procedures. Participants meeting eligibility criteria will be assigned a subject identification number during the baseline visit. Study participants will continue to receive standard treatment for OUD following prescriber-recommended instructions for medication formulation and starting dose, as well as clinic visits unrelated to the study (eg, for medication management or counseling). Standard treatment will be supplemented with the therapeutic tools (PEAR-002b and reSET-O).

Participants will be enrolled for 4 weeks to assess the acceptability and ease of use of the PDT. At baseline, if participants still meet all inclusion and exclusion criteria, study staff will provide them with a phone preloaded with the study apps. Participants will be asked if they also agree to wear the EmbracePlus smartwatch for the duration of the study, and those who agree will be provided the device. Study staff will train willing participants in use of the study apps and the EmbracePlus device. Additionally, a UDS will be performed, and the Clinical Opiate Withdrawal Scale (COWS) will be used. One week later, the participant will return to the clinic and complete a survey and an interview. Study staff will conduct another UDS, administer the COWS, and ask about any adverse events (AEs) or side effects. Following this visit, the participant will return weekly for a UDS and AE assessment. At week 4, the participant will return for a UDS and complete a final survey and exit interview. Primary, secondary, and exploratory objectives and end points are outlined in Textbox 1.

Study objectives and end points.
**Primary objectives**
To assess the effect of PEAR-002b on home buprenorphine initiation success rates (ie, the proportion of participants attending the post–buprenorphine initiation visit)To evaluate the acceptability of PEAR-002bTo assess the effect of PEAR-002b on medication adherence rates
**Primary end points**
Proportion of participants attending the post–buprenorphine initiation visit and the proportion of participants who experience buprenorphine initiation–related adverse events (eg, precipitated withdrawal)Participants’ ratings of PEAR-002b for ease of use, satisfaction, perceived helpfulness, and the likelihood they would recommend itParticipant self-report data and confirmation by urine drug screens
**Secondary objectives**
To assess dosing and engagement of participants with PEAR-002bTo evaluate the contingency management reward structure
**Secondary end points**
Participants’ use patterns of PEAR-002b, including lesson completion, self-report assessment completion, voluntary use of self-report features, and response to notificationsParticipant interviews and user satisfaction surveys
**Exploratory objectives**
To evaluate the preliminary efficacy of PEAR-002bTo evaluate compliance with wearing the EmbracePlus deviceTo evaluate the feasibility of using digital biomarkers to predict withdrawal, craving, and opioid use
**Exploratory end points**
Abstinence from illicit opioids and medication adherence, measured by urine drug screens, and retention in treatment, measured by time to dropout (if applicable)Device wearing time (eg, total hours worn and average percentage of time worn per day) measured by the devicePrediction power based on physiologic data (eg, heart rate and skin conductance) collected via the device

### Demographics

Demographic information to be collected includes age at time of consent, sex, gender, race and predominant ethnicity, level of education, marital status, employment status, income, number of children, health insurance status, involvement in the criminal justice system, distance of residence from treatment site (in miles), and usual method of transportation.

### Medical and Medication History

Relevant medical history and current medical conditions will be collected, including current or prior treatments received for mental health disorders, hepatitis C, HIV, and chronic pain syndromes. History of substance use will be collected for the following categories: opioids, cocaine, stimulants other than cocaine, alcohol, marijuana, benzodiazepines, and other substances. Data to be collected regarding each substance include onset of use, number of years used regularly, amount used, type used (eg, pill vs powder), route of use, history of overdose, and longest period of abstinence. History of substance use treatment will also be collected, including present and prior treatment, type of treatment facility, number of treatment episodes, and current recovery activities. Nicotine use history will also be collected, including type, route, quantity, duration of use, and prior use. Medication history will include the name, dose, frequency, start and stop dates of the medication, and the indication for use. Prior experience with medication for substance use disorder/OUD will also be recorded.

### Evaluation of Phone Use

Study staff will evaluate participants’ comfort level with using smartphones and navigating through common apps.

### Interviews and Surveys

Interviews with participants will be conducted by study staff to evaluate their experiences with the PDT, particularly its ease of use and acceptability. Interviews may be performed in person or remotely via video or phone. These sessions may be recorded for transcript generation if informed consent is obtained from the participant, investigator, or both. Participant surveys will be completed by participants per the assessment schedule. Table 1 shows a schedule of study assessments.

**Table 1 table1:** Schedule of study assessments.

Procedure/measure	Baseline	Post–buprenorphine initiation	Maintenance		End of study
Timepoint	Week 0 (day 0)	Week 1 (day 7, plus or minus 2 days)	Week 2 (day 14, plus or minus 2 days)	Week 3 (day 21, plus or minus 2 days)	Week 4 (day 28, plus or minus 7 days)
Informed consent	✓				
Inclusion/exclusion	✓				
Mobile use evaluation	✓				
Demographics	✓				
Medical history	✓				
Medication list/history	✓				
EmbracePlus monitor recording	✓	✓	✓	✓	✓
Urine drug screen	✓	✓	✓	✓	✓
Adverse events and side effects assessments		✓	✓	✓	✓
Clinical Opiate Withdrawal Scale	✓	✓			✓
Participant survey		✓			✓
Participant interview		✓			✓
Medication list changes		✓	✓	✓	✓
Timeline Followback Assessment	✓	✓	✓	✓	
Protocol deviations	✓	✓	✓	✓	✓

### Data Management, Study Oversight, and Monitoring

Designated staff from the study sponsor (the study monitor) will review the e-CRFs entered by study staff for completeness and accuracy. Authorized study staff will respond to queries and make any necessary changes to the data. Oversight of data management, including data collection, storage, and export; security; tracking; data analysis; and quality assurance will be the responsibility of the sponsor. The study investigator will ensure the accuracy, completeness, and timeliness of the data reported to the sponsor and be responsible for ensuring that all study staff adhere to human subjects/IRB guidelines related to data management. Data files will be backed up at regular intervals and will be accessible only by trained study staff members.

The study monitor will ensure that the research is conducted and documented according to the protocol and in accordance with the guidelines for Good Clinical Practice. Virtual study monitoring visits will be conducted at appropriate times during the study per the monitoring plan.

### AE Reporting

The investigator or designee and research site staff are responsible for the detection, documentation, classification, reporting, and follow-up of events meeting the definition of an AE or serious AE (SAE). Spontaneously reported or observed AEs will be recorded throughout the study beginning at the time the participant gives informed consent. AEs will be elicited using a nonleading question at designated time points. Regardless of seriousness, intensity, or presumed relationship to PEAR-002b, all AEs will be recorded in the source documentation from the time of consent until the end of the last study visit. AEs that occur after screening and prior to implementation of PEAR-002b will be recorded in the source documentation under medical history. AEs occurring after baseline and until the last study visit, known as treatment-emergent adverse events (TEAEs), will be recorded in the AE page of the e-CRFs. All measures required for management of TEAEs will be recorded in the source documentation. The investigator will be responsible for informing the IRB and regulatory authorities of SAEs, as required by local and regional regulations.

### Statistical Analysis Methods

This feasibility study is largely exploratory, with several end points focused on measuring participant satisfaction, attitudes, and use of the mobile app component of reSET-O and PEAR-002b. Therefore, many of the statistical analyses will be descriptive and will involve computing and reporting measures of central tendency (ie, mean and median) and variability (ie, variance and standard deviation) for the variables of interest. These statistics will highlight which aspects of the therapeutic and the experience are helpful and engaging to participants, and which aspects are less engaging.

#### Primary End Points

Home buprenorphine initiation success will be summarized as the proportion of participants attending the post–buprenorphine initiation visit (week 1) and the proportion of participants who experience buprenorphine initiation–related AEs (eg, precipitated withdrawal). Acceptability of PEAR-002b will be evaluated based on individual participants’ ratings of ease of use, satisfaction, perceived helpfulness, and likelihood of recommending PEAR-002b. Descriptive statistics will be performed on Likert-scale and multiple-choice items that assess user satisfaction and attitudes about the app. Analyses will be conducted on data collected at each assessment point throughout the study, ratings over the course of the study, and for overall user satisfaction as measured at the end of the study. Medication adherence will be evaluated by participant self-report data and confirmed by UDS (ie, a positive result for buprenorphine and norbuprenorphine). UDS data will be summarized as means of individual participants’ proportion of total urine samples testing positive for buprenorphine or norbuprenorphine over the 4-week study.

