### Study Design

This will be a qualitative observational cohort study with a recruitment goal of 10 adults with OUD (inclusion and exclusion criteria are listed below).

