### Exclusion Criteria

Study exclusion criteria are as follows: currently on methadone or naltrexone pharmacotherapy; currently on buprenorphine MOUD treatment; planning to move out of the geographic area within 2 months; insufficient English fluency to participate in the consent process, intervention, or assessment; inability to comply with study procedures due to physical or mental condition; currently receiving inpatient treatment for OUD; and pregnancy.

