#### Exploratory End Points

Abstinence will be defined by participant self-reports and confirmed by the absence of opioids (other than buprenorphine) in the UDS. UDS data will be summarized as means of individual participants’ proportion of total urine samples testing negative for opioids other than buprenorphine over the 4-week study. Treatment retention will be measured as time to drop-out (defined as the last face-to-face contact with a participant) and analyzed using the Kaplan–Meier method.

Feasibility and acceptability of EmbracePlus will be assessed by measuring the total hours and percentage of weeks wearing the device. Week-by-week averages and the total number of hours across all weeks will be assessed. Acceptability will be evaluated based on participants’ ratings of ease of use and satisfaction with EmbracePlus. Descriptive statistics will be calculated for Likert-scale and multiple-choice items that assess user satisfaction and attitudes about EmbracePlus. If physiologic data are sufficient, multiple statistical learning models will be used to evaluate if these models have sufficient power to predict withdrawal or opioid use events in advance, levels of cravings, or both.

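### The urine-screen denominator does not set aside the day-0 sample, so read literally it scores a fully adherent completer 80% rather than 100%

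*Protocol article*

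**What the plan says.** In the protocol article, Statistical Analysis Methods, Primary End Points, adherence is judged by self-report and confirmed by urine drug screen. The urine data are summarised as the mean of each participant's "proportion of total urine samples testing positive for buprenorphine or norbuprenorphine over the 4-week study". The Methods part of the Abstract gives the same rule. Under Exploratory End Points, abstinence is summarised as the mean of each participant's "proportion of total urine samples testing negative for opioids other than buprenorphine over the 4-week study".

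The sample schedule is given in three places:

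- Table 1 ticks the urine drug screen at week 0 (day 0) and at weeks 1, 2, 3 and 4.
- The compensation paragraph under Confidentiality lists "urine sample (n=5), $10", separately from "weekly study visit (n=4), $20". That is one more urine sample than there are weekly visits.
- Study Procedures and Assessments describes the baseline visit at which the phone with the study apps is handed over: "Additionally, a UDS will be performed, and the Clinical Opiate Withdrawal Scale (COWS) will be used". The post-initiation visit comes a week later.

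The Exclusion Criteria rule out people "currently on buprenorphine MOUD treatment".

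**The concern.** The day-0 sample is taken before the treatment whose adherence is being measured. In a person who is not on buprenorphine it should be negative however well that person later takes the medication. Counting it therefore adds a near-certain failure to every participant's score. The same applies to abstinence wherever the day-0 sample contains other opioids, since it describes use before treatment began.

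Adherence is one of three primary objectives, and the Discussion says the data may inform larger studies. A reader who meets a mean of 80% would take it as one sample in five missing the drug during treatment, when it could equally be the arithmetic result of perfect adherence. With 10 participants and no comparator arm, nothing else in the study would reveal the offset.

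**Working it through.** The article states no adherence figure, so there is none to reproduce. The check is arithmetic on the schedule.

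**Inputs**
- Scheduled samples per participant: 5, of which 4 are post-baseline (Table 1; compensation paragraph).
- Participants: "recruitment goal of 10 adults with OUD" (Study Design).
- Baseline buprenorphine result: taken as negative, because current buprenorphine treatment is an exclusion. Non-prescribed use is not excluded, so a positive share q is varied below as an assumption.
- Dropout: the article gives no rate, so the numbers used are assumptions.

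**Ceiling for a completer.** With all 4 post-baseline samples positive and the baseline sample counted, the highest mean is (4 + q)/5.
- q = 0: 4/5 = 80%
- q = 0.1: 4.1/5 = 82%
- q = 0.2: 4.2/5 = 84%
- q = 0.3: 4.3/5 = 86%

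With baseline set aside it is 4/4 = 100%. Below the ceiling the shrinkage is proportional: if true post-baseline positivity is 90% and q = 0, the literal rule reports 0.9 × 4/5 = 72%.

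For abstinence the same formula holds with q as the share of baseline samples negative for other opioids. The ceiling is 80% if every baseline sample is opioid-positive, and 82% to 86% if 10% to 30% are negative. All of these are assumptions.

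**Scheduled or provided samples.** The text does not say which the total means. For a participant positive at each of k attended post-baseline visits and then lost, with a negative baseline sample:

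| k | provided, with baseline: k/(k+1) | scheduled, with baseline: k/5 | provided, weeks 1–4: k/k | scheduled, weeks 1–4: k/4 |
|---|---|---|---|---|
| 0 | 0% | 0% | undefined | 0% |
| 1 | 50% | 20% | 100% | 25% |
| 4 | 80% | 80% | 100% | 100% |

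Now take an illustrative cohort of 10: 6 completers with every post-baseline sample positive, 3 lost after a positive week-1 sample, and 1 who never returns.
- Provided, with baseline: (6 × 0.8 + 3 × 0.5 + 0)/10 = 63%
- Scheduled, with baseline: (6 × 0.8 + 3 × 0.2 + 0)/10 = 54%
- Provided, weeks 1–4: 9/9 = 100%, with one participant undefined
- Scheduled, weeks 1–4: (6 × 1 + 3 × 0.25 + 0)/10 = 67.5%

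The same data give anything from 54% to 100%, depending on two choices that the wording leaves open.

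**The case against.** The strongest reply is that no sentence says the baseline sample counts. The payment list and Table 1 describe collection and do not define an analysis denominator. Table 1 labels day 0 as week 0, apart from weeks 1 to 4, so a four-week study could be read as those four weeks, and then there is no ceiling. This stands in part: 80% follows from the literal reading and is not a stated rule. It does not clear the text, because nothing takes day 0 out of a total that the schedule puts at five. The AE Reporting section does limit treatment-emergent events to those after baseline; the urine summaries carry no such limit.

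A reader might go further and infer that the plan discards missed samples, so that dropout distorts the mean in a known direction. The article does not support that. It is silent on scheduled versus provided, and a missed-sample rule may properly sit in an analysis plan that is not shown. The direction also depends on the reading: a person lost after one positive week-1 sample scores 50% if provided samples include baseline and 100% if they do not.

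A reader might also infer that abstinence is capped in the same way by design. It is not, since no entry criterion requires an opioid-positive urine.

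Finally, this is a small, uncontrolled, largely descriptive pilot. Adherence also rests on self-report, attrition is shown by week-1 attendance and a Kaplan–Meier retention analysis, and each sample is tied to a visit, so a weeks 1–4 figure could be recomputed later. All of that is correct. It lowers the severity but does not remove the point.

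**Conclusion.** The concern holds for the baseline sample. Followed literally, the stated rule for a primary end point counts a pre-treatment sample and gives a fully adherent completer 80%. The ceiling on the mean rises to 82% to 86% if 10% to 30% of participants are already buprenorphine-positive at baseline. For abstinence the effect is conditional on opioid-positive baseline samples.

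The scheduled-or-provided question is an ambiguity worth settling in the same edit, not a separate error. It would be too strong to conclude that the results cannot be used in a larger study, because the visit-level data allow the figure to be recalculated. Severity is moderate: no test, threshold or go/no-go rule depends on this mean, but the published number would be misread.

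**What to change.** In the Abstract, Primary End Points and Exploratory End Points, redefine the summary as the mean over participants of the share of the four scheduled post-baseline samples (weeks 1 to 4) that are positive for buprenorphine or norbuprenorphine (adherence), or negative for other opioids (abstinence), with a sample not provided counted as not confirmed. Beside it, give the version based on provided weeks 1–4 samples, with the number of participants contributing, since anyone who never returns has no value there. Report the week-0 result separately as a baseline characteristic.

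The cost is one sentence in each place and no new data. The small downside is that the scheduled version mixes retention into adherence, and retention is already its own exploratory end point. Showing the provided-samples figure alongside lets a reader separate the two.
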